### Assessment instruments

3.4

In the following, all assessment instruments are described in detail. There are three different sets of assessment instruments in this study: (1) the baseline survey completed by each participant prior to the start of the study; (2) the journaling entries completed at each measurement time point during the 14-day assessment period; and (3) the daily surveys completed at each measurement time point during the 14-day assessment period, which serve as ground truth for predicting the content of the journaling entries (target vaiables).

#### Baseline survey

3.4.1

Prior to the start of the study, participants will complete several baseline questionnaires: a demographic questionnaire capturing medication use and health history (see Additional file 1 of the Supplementary Material to this article), an educational level questionnaire based on the International Standard Classification of Education—Fields of Education and Training 2013 [49], and the WHO-5 Well-Being Index (WHO-5) [50] assessing general well-being. In addition, mental health and stress will be evaluated using the 21-item Depression Anxiety Stress Scales (DASS-21) [51], while dispositional self-control will be measured with the Brief Self-Control Scale (SCS-K-D) [52]. All instruments were administered in their validated German versions.

#### Daily journaling

3.4.2

During the 14-day study period, participants will be prompted each evening via the messenger service to record a voice message reflecting on the day’s highlights and lowlights. The standardized instruction will be: “What were your high- and lowlights of the day? How did they make you feel and why?” This prompt is intended to facilitate reflection on both positive and negative experiences. In contrast to stream-of-consciousness instructions (e.g., “Write about your day”), which may yield brief responses, this question is expected to elicit more elaborated entries. By addressing overall emotional well-being, it allows for a broad spectrum of emotions to be captured, rather than restricting the focus to a single emotional dimension as in approaches such as gratitude journaling or expressive writing. No constraints will be imposed on entry length, thereby enabling participants to provide responses of natural scope without artificial extension.

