### Procedure

3.3

Upon completion of enrollment, participants will be welcomed by the study team within the app and prompted to complete the baseline assessment questionnaires. For this purpose, they will receive an individualized link via the messenger service to an online survey hosted on the SoSci Survey platform^2^, which can be accessed through their smartphone browser. The link will contain each participant’s unique code to ensure accurate data assignment. The survey will cover demographics, education, general well-being, mental health, stress, and dispositional self-control, and is expected to take no longer than 10 to 15 min to complete. Subsequently, participants will be randomized into two groups using block randomization with randomly varying block sizes of 4, 6, and 8 to ensure approximately equal distribution. To generate the list of group assignments, the tool Sealed Envelope [48] is used. Participants are then assigned based on their registration sequence. The type group will be instructed to consistently type their journal entries, whereas the speak group will be instructed to record their journal entries as voice messages via the messenger service. In order to establish a “neutral voice” baseline for each participant in the speaking group, they will be asked to read standardized text snippets from the literature on voice assessment.^3^ These snippets are designed to avoid eliciting emotion or cognitive load.

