During the 14-day study phase, participants will be asked to record a daily journal entry as a (voice) message in the messenger service app, sharing their “high- and low-lights” of the day by either typing or speaking according to their group assignment. They will receive a notification via the messenger service around 6 p.m., but the assessment may be completed at any time during the remainder of their day. Immediately after creating the journal entry, participants will be asked to complete a short reflective survey on the SoSci Survey platform, accessed via an individualized link provided in the reminder message. Since the links will be personalized, all reminders will be sent individually and manually by the study team. The sequence—first journaling, then completing the questionnaire—is chosen to ensure that participants can report naturally on topics they consider relevant, without potential bias introduced by answering questionnaires beforehand. All questionnaire scores will serve as ground truth reference values for training and evaluating the NLP models. The total time required for journaling and survey completion is expected to be approximately 5–10 minutes per day. Each daily data point will include a journal entry, three emotional well-being metrics, a daily stress level, a measure of situational self-control, and a list of topics mentioned in the journal entry. To enhance compliance, the study team will monitor on a daily basis whether participants have completed the required assessment. If an assessment is missed or remains incomplete from the previous day, a reminder will be sent in the afternoon notifying the participant of the missed entry. The reminder will also include a brief question regarding the reason for the omission, along with an encouragement to complete the assessments on subsequent days. After the two-week study period, participants will receive individualized feedback based on their journal entries and questionnaire responses (see Section 3.5 for more detail). Providing it once at the end of the study was intended as an incentive to complete the two weeks. As a final step, participants will be asked to complete a feedback questionnaire to provide direct evaluations of their study experience. In addition, focus group sessions with voluntary participants will be conducted to further explore participant perspectives (see Section 3.6 for further details).

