#### RQ1: NLP analysis

4.2.2

The spoken journal entries will be transcribed using Whisper [65]. All journal entries will be preprocessed according to standard NLP procedure (tokenization, lowercasing, lemmatization, and stop-word removal) to generate sparse representations [e.g., term frequency–inverse document frequency; TF–IDF). Additionally, dense representations (e.g., contextual embeddings from German pre-trained transformer-based models like GBERT [66] or German-BERT [67]] will be generated. Here, preprocessing will be limited to the model-specific tokenization procedure.

The comparison of architecture classes is itself part of the study, as prior literature has not yet established a best-performing architecture for journaling data. Therefore, different supervised machine learning models will be employed for this regression task, ranging from classical approaches (e.g., random forest regression or support vector regression) to transformer-based deep learning models (e.g., BERT-based regression head). Separate predictive models will be trained on the above-mentioned representations for each outcome variable (MDBF subscales, PSS-4). We will additionally evaluate end-to-end fine-tuning of a smaller transformer model (e.g., a distilled German BERT variant), which will operate directly on tokenized journal entries rather than precomputed representations. Here, we acknowledge the higher risk of overfitting compared to our main representation-based approach.

As a baseline, a mean predictor will be implemented. Model performance will be quantified using root mean squared error (RMSE) and mean absolute error (MAE) to capture prediction error magnitude, and Pearson correlation to assess the strength of association between predicted and observed scores. All models will be evaluated using k-fold cross-validation. To account for repeated measures within participants, cross-validation will be conducted at the participant level, such that all entries from a given participant are assigned exclusively to either the training set or the test set. To examine group differences, models will be trained and evaluated separately for the written and transcribed groups. Predictive performance metrics will then be compared across groups. Differences in performance will be formally tested using bootstrapped confidence intervals to provide robust inference without assuming normality of error distributions.

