#### RQ3: compliance and self-control analysis

4.2.4

Compliance will be defined as daily completion of both the journal and questionnaire (0 = not completed, 1 = completed) across the 14-day study period. Daily compliance will be analyzed using a mixed-effects logistic regression with fixed effects for group, day, trait self-control (SCS-K-D), mean state self-control (SSCCS), their relevant interactions, and a random intercept for participants to account for repeated measures. Spearman’s rank correlation will be used descriptively to assess the association between trait self-control and total journals completed.

To predict on a global level whether participants will drop out (0) or complete the study (1), a logistic regression will be performed with trait self-control (SCS-K-D) and mean state self-control (SSCCS) as predictors of study completion. The study will be considered completed if participants submit the feedback questionnaire at the end of the study.

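### Section 3.4.2 words the daily prompt as a voice-message request for all participants, and no listed daily variable would reveal dictated or read-out entries in the typed-versus-spoken comparison

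*Protocol article*

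**What the plan says.** Section 3.4.2 (Daily journaling) states that "participants will be prompted each evening via the messenger service to record a voice message". Nothing in that sentence restricts it to one group. The standardised question that follows it asks about the day's good and bad moments and the feelings attached to them, and names no input modality.

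Elsewhere the modality is set by group. Section 3.1 has one group recording and the other typing. Section 3.3 (Procedure) says "The type group will be instructed to consistently type their journal entries", while "the speak group will be instructed to record their journal entries as voice messages via the messenger service", and describes the daily entry as made "by either typing or speaking according to their group assignment".

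Section 3.3 also lists what is collected each day: "Each daily data point will include a journal entry, three emotional well-being metrics, a daily stress level, a measure of situational self-control", plus the topics mentioned. Section 3.4.3 describes the daily survey with the same content. Daily supervision concerns completion: "the study team will monitor on a daily basis whether participants have completed the required assessment". Section 4.2.4 does the same for RQ3: "Compliance will be defined as daily completion of both the journal and questionnaire".

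For RQ1, section 4.2.2 says that "models will be trained and evaluated separately for the written and transcribed groups", after which the performance metrics are compared between groups.

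**The concern.** Input modality is the only thing randomised, and the typed-versus-spoken difference in prediction accuracy is part of the primary hypothesis (section 2). The section that defines the journaling instrument should therefore state the modality correctly for both groups, and 3.4.2 does not.

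The second issue is what the data can show. Participants use their own smartphones and one messenger. A type-group participant who dictates through the phone keyboard produces speech that arrives as text and is analysed as typed. A speak-group participant who reads out a prepared draft produces written language that arrives as audio and is analysed as speech. The introduction motivates the comparison by the more deliberate and structured character of written text, and both behaviours blur that distinction. The Discussion (section 5) accepts that people probably differ in the mode they prefer and recommends free choice in future, so a motive for departing from the assigned mode is foreseeable.

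At stake is how a null or small RQ1 difference is read: as a finding about modality, or as the result of entries not made in the way assigned. An analysis plan written later can set handling rules, but it cannot create a variable that was never collected.

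**Working it through.** **Step 1: the wording, side by side.**

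| Place | Type group | Speak group |
|---|---|---|
| 3.1 Design | types | records |
| 3.3 Procedure, group instruction | types every entry | voice message |
| 3.3 Procedure, daily entry | by assignment | by assignment |
| 3.4.2, sentence introducing the prompt | voice message | voice message |
| 3.4.2, the standardised question itself | no modality named | no modality named |

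Only one sentence is out of line, and only for the type group.

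**Step 2: which departures could be seen.** Section 4.3.2 says voice recordings are collected in the messenger, and section 4.2.2 says spoken entries are transcribed with Whisper. Each entry therefore arrives as text or as audio.

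| Departure | Arrives as | Visible? |
|---|---|---|
| Type group sends a voice message | audio | yes, from the format |
| Speak group sends a text | text | yes, from the format |
| Type group dictates via the keyboard | text | no |
| Speak group reads out a draft | audio | not in any listed variable |

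For the first two rows, all that is missing is a stated handling rule, which an article may leave to the full protocol or analysis plan. For the last two, the article enumerates the daily data point (3.3) and the daily survey (3.4.3), and mode of production is in neither. A listener might suspect reading from a recording, but that is a judgement and no such check is described.

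**Step 3: the plan's own figure.** Section 4.1 gives D = 500 data points per group, d = 14 days and r = 28% dropout.

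N = D / (d × (1 − r)) = 500 / (14 × 0.72) = 49.6, rounded up to 50 per group. This reproduces. Expected entries per group: 50 × 14 × 0.72 = 504. Nothing proposed here changes either number.

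**Step 4: direction, and an illustration of size.** Let f be the share of type-group entries that are really spoken language, and m the share of speak-group entries that are really written language. For a language feature with mean μT in true typing and μS in true free speech:

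- type-group mean = (1 − f)μT + fμS
- speak-group mean = (1 − m)μS + mμT
- difference = (1 − f − m)(μS − μT)

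The shares are assumptions, because the documents give none.

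| Assumed share | Entries of 504 affected in a group | Feature contrast kept, type group only (m = 0) | Kept, both groups (m = f) |
|---|---|---|---|
| 5% | about 25 | 95% | 90% |
| 10% | about 50 | 90% | 80% |
| 20% | about 101 | 80% | 60% |

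The factor applies to mean language features. RQ1 compares RMSE, MAE and Pearson correlation from models trained separately by group, and these need not move in proportion to the mixture. The table shows direction and order of magnitude for features, not the loss in the RQ1 contrast.

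**The case against.** The strongest reply is that 3.4.2 is loose narration and not evidence of what participants receive. The question actually put to them names no modality, and the group instructions in 3.1 and 3.3 are clear. That stands: a reader might infer that every participant is really asked for a voice message, and the documents taken together do not support this.

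A reader might also infer that any off-modality entry is undetectable. That is wrong for plain crossovers, which show as text or audio and pass under staff who look at each participant daily.

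Third, the type group is already told to type consistently, and the instructional video, the full participant instructions or the end-of-study questionnaire in the supplement may deal with dictation. None of these is shown, so this cannot be excluded. An instruction would reduce the problem. A single item at the end of the study would not label individual entries.

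Fourth, dictated text appears on screen and can be edited before sending, so it is not the same as a transcribed voice message. This is fair, and it is a further reason not to put a number on the effect.

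Finally, restricting the analysis to assigned-modality entries selects on behaviour after randomisation and shrinks a data set sized at about 500 entries per group. This limits that analysis to a supporting role.

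**Conclusion.** Two things hold. Section 3.4.2 contradicts 3.1 and 3.3 on the randomised factor and must be reconciled; it is most likely a slip. And the listed daily data cannot identify keyboard dictation in the type group or reading from a draft in the speak group, and this cannot be made good once the 14 days are over.

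Such entries would be expected to bias the typed-versus-spoken contrast in RQ1 towards no difference. This assumes that dictated text resembles speech and that read-out text resembles writing, at least in part. The documents do not allow the amount to be calculated: they give no off-modality rate, and the mixture factor does not carry over directly to RMSE, MAE or correlation. A reader might take the illustrative shares as an established loss of the primary contrast; they are not. Nor do the documents show that dictation or reading out will occur.

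Defining RQ3 compliance as completion, whatever the modality, is a legitimate choice and is not faulted here. The sample size is unaffected. This is a cheap improvement that would make the primary comparison easier to interpret, not a flaw that invalidates it.

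**What to change.** 1. Reword section 3.4.2 by group, so that the type group is prompted to type and the speak group to record, in line with 3.1 and 3.3.
2. Tell the type group not to use keyboard dictation and the speak group not to read from a draft.
3. Log the message type (text or audio) of each entry, and add one tick item to the daily survey on how the entry was made: typed, dictated, spoken freely or read out.
4. Keep the comparison by randomised group as the main RQ1 analysis. Add a sensitivity analysis limited to entries made in the assigned modality, stating that it selects on post-randomisation behaviour and uses fewer entries.

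The cost is a wording change, a few seconds of extra daily burden and one additional analysis. The target of 50 participants per group stays as it is.

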#### Daily target variables

3.4.3

The daily surveys will include the Multidimensional Mood State Questionnaire (MDBF), a parsimonious six-item mood scale designed for momentary assessment in daily life to evaluate participants’ well-being [53]. This instrument is derived from the German-language Multidimensional Mood Questionnaire (MDMQ) [54] and captures three dimensions: valence (good–bad mood), arousal (wakefulness–fatigue), and calmness (calmness–restlessness). Scores range from 1 (bad mood, fatigue, restlessness) to 7 (good mood, wakefulness, calmness). In addition, the ecological momentary assessment version of the Perceived Stress Scale-4 (PSS-4) [55] will be administered to assess daily stress levels. Both the MDBF and the PSS-4 will be adapted to refer to the entire past day rather than the immediate moment of completion. This adaptation will ensure consistency with the journaling entries, which also cover the whole day, thereby enabling the questionnaire scores to be meaningfully predicted from the entries by the NLP models. Furthermore, participants will answer two questions from the State Self-Control Capacity Scale (SSCCS) [56] to assess their situational self-control when journaling.^4^ Finally, participants will also select from a predefined list the topics mentioned in their journal entry. The possible topics are adopted from a North American study on diary content [57] and translated into German: movement, family, food, friends, religion/spirituality, health, love, recreation, school, sleep, and work. The term “religion/spirituality” will be used instead of “god,” as religion is practiced less centrally in European countries compared to North America [58].

### Individual feedback

3.5

After the two-week journaling assessment period, participants will receive written feedback of their provided data in the form of a PDF document (see Additional file 2 of the Supplementary Material to this article) delivered via the messenger service, based on their completed psychopathological questionnaires and journaling entries. The feedback will be generated with Python and include the following elements:
Overview of the demographics describing the study population.Explanation, evaluation, and interpretation of the baseline questionnaires. Since the WHO-5 and the SCS-K-D do not provide a direct interpretation of their scores, averages from the German population were provided for comparison.A heat map and a line chart visualizing the MDBF values over time; the former based on the original scale of the questionnaire and the latter centered on the individual mean. Person-mean centering will be applied to make the questionnaire scores more interpretable for participants, with 0 reflecting each participant’s average for a given dimension. Negative scores will indicate worse-than-average scores, while positive scores will indicate better-than-average scores.A line graph visualizing the PSS-4 score over time, centered on the individual mean.A pie chart visualizing the distribution of the mentioned topics.Four times a bar chart showing the valence values of the MDBF over time, while centered on the individual mean. Individual charts will be colored according to the occurrence of the four most-mentioned topics. If the topic is mentioned on a day, the bar will be colored orange; otherwise, it will be colored gray. This should allow identifying relations between valence and topics.Three word clouds: one over all journal entries, one with words from the days with positive MDBF valence scores centered on the individual’s average, and one from the negative days. This should allow insights into predominant topics for better and worse days. In a pre-processing step, stopwords will be removed using Natural Language Toolkit (NLTK) [59].All (transcribed) journal entries with date and time.The feedback will conclude with a list of contact addresses for support services and assistance, and participants will be reminded that they may contact the study team at any time with questions regarding the feedback. In addition, participants whose DASS-21 scores exceed the respective cutoff values and who meet the age eligibility criteria will receive information about an additional study that offers access to psychological counseling.It should be noted that the feedback is based solely on each participant’s self-report data and does not incorporate any insights derived from the NLP analyses. This approach ensures that participants receive feedback that is independent of AI and remains accurate and meaningful even if model performance is suboptimal. The goal is to evaluate the capability of NLP models to infer indicators of users’ mental health (mood and stress), such that future studies may incorporate automatically generated feedback that includes these assessments. Should participants have questions about the feedback or feel uncertain or distressed by any of the information provided, they will be able to contact the study team for clarification and support.

### Participants involvement

3.6

As part of a participatory research approach, students will have the opportunity to provide direct feedback to the study team in order to evaluate the different types of feedback, indicate their preferred input modality, and critique the study. For this purpose, participants will be asked at the end of the study to complete a feedback questionnaire, which is provided in the Additional file 1 of the Supplementary Material to this article. Responses will be recorded using a 7-point Likert scale ranging from 1 (not at all) to 7 (very much)^5^. The questionnaire will consist of 23 quantitative items and 19 open-ended questions, all of which will be mandatory.

To gain a deeper understanding of participants’ opinions and to obtain richer insights into their attitudes, experiences, and perspectives regarding their motivation, needs, and potential barriers related to the study, two guided qualitative focus group interviews with three to four participants will be conducted. The participation will be voluntary. For this purpose, a focus group guideline (see the Additional file 3 of the Supplementary Material to this article) will be collaboratively developed within the research team. The guideline will address several relevant topics, including motivation for study participation, reflections on the scope and feasibility of the assessments, completion of questionnaires, individual feedback after measurement points, the anticipated impact of the study on daily life, and suggestions for possible modifications to the study design.

